# Yinma Jiedu granules combined with antibacterial drugs for patients with community-acquired pneumonia: protocol for a multicenter, randomized, double-blind, placebo-parallel controlled clinical trial

**DOI:** 10.3389/fmed.2025.1612945

**Published:** 2025-09-09

**Keywords:** community-acquired pneumonia, randomized controlled trial, Yinma Jiedu granules, Chinese patent medicine, clinical symptoms

## Abstract

**Background:**

Community-acquired pneumonia (CAP) is a severe respiratory infection that can lead to a range of health issues. Yinma Jiedu (YMJD) granules, a representative classic traditional Chinese patent medicine, are widely used in China, yet high-quality evidence regarding their efficacy in alleviating clinical symptoms remains limited. This study aims to evaluate the efficacy and safety of YMJD granules for the treatment of CAP.

**Methods:**

This multicenter, randomized, double-blind, placebo-controlled parallel clinical trial will be conducted at 11 hospitals in China, with each center enrolling patients competitively. A total of 226 CAP patients who meet the inclusion criteria will be stratified by age and then randomized in a 1:1 ratio to the intervention group (*n* = 113; YMJD granules) or control group (*n* = 113; YMJD placebo). All patients will receive a 7-day treatment course followed by a 7-day follow-up for assessment. The primary outcome is the clinical symptom improvement rate on day 4. Secondary outcomes include the clinical cure rate, the improvement rate of individual symptoms, the Cough and Sputum Assessment Questionnaire, the improved pneumonia imaging absorption evaluation scale, the CURB-65 score, the dosage and course of antibiotics, the changes in inflammatory markers, Traditional Chinese Medicine (TCM) syndrome scores and the amount of emergency drug used. Adverse events will also be assessed. Subgroup analyses will explore heterogeneity in YMJD treatment effects.

**Discussion:**

This trial is the first large-sample, randomized, double-blinded, placebo-controlled study of YMJD granules in patients for CAP. It aims to elucidate the mechanisms of early symptoms improvement, identify optimal patient populations, and informing new therapeutic strategies.

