#### Primary outcome

2.5.1

##### Clinical symptom improvement rate on day 4

2.5.1.1

The primary outcome is early clinical response, defined as an improvement in at least two of four symptoms (cough, chest pain, sputum production, dyspnea) without any exacerbation of any symptom within 96 h following the initial dose of study medication in the intention-to-treat population (24).

An improvement in symptoms is defined as a reduction in severity by a minimum of one grading level. Refer to Table 2 for details.

**Table 2 tab2:** Community-acquired pneumonia symptom severity assessment scale.

Symptoms	Asymptomatic	Mild	Moderate	Severe
Cough	No cough	Coughing, but does not interfere with daily activities	Frequent cough that interferes with daily activity	Coughing day and night, most daily activities limited, sleep disrupted
Expectoration	No expectoration	Mild expectoration	Moderate expectoration	Excessive expectoration
Pleurisy pain	No pneumonia-related chest pain	Occasional chest pain during deep breathing, but does not interfere with daily activities	Chest pain during normal breathing, affecting daily activities	Chest pain occurs during rest or shallow breathing, and most daily activities are limited
Dyspnea	No dyspnea	Shortness of breath during intense activities, but does not interfere with daily activities	Frequent dyspnea that interferes with daily activity	Dyspnea occurs during mild activity or at rest, and most daily activities are limited

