##### Changes in inflammatory indicators

2.5.2.7

Evaluate the improvement of systemic infection indicators in two groups of patients on day 1 and day 7 of enrollment, including C-reactive protein, serum procalcitonin, interleukin 6, serum amyloid A.

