### Sample collection

2.6

Blood samples (standard EDTA blood collection) will be collected on day 1 and day 7; these will be subsequently centrifuged to separate plasma and serum, and samples will be frozen at −80 °C.

Sputum samples will be collected from each patient sputum induction using hypertonic saline is performed if participant unable to expectoration, based on Chinese national guideline on diagnosis and management of Cough (30).

All of biological samples will be used for muti-omics analysis to explore the biological mechanisms of YMJD.

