### Participant timeline

2.8

Patients in the trial are required to be recorded four times, with visits at enrollment, day 4, day 7 and day 14. The specific assessments at each visit are detailed in Table 4.

**Table 4 tab4:** Time schedule of enrolment, intervention and outcome measures of the trial.

Study phase	Treatment phase			Follow-up phase
Study day	Day 1	Day 4	Day 7	Day 14
Basic medical history				
Informed consent form	X			
Basic condition	X			
Treatment history	X			
Past medical history	X			
Allergy history	X			
Concomitant medications		X-------------------------------------------X		
Efficacy evaluation				
Chest CT	X		X	
C-reactive protein	X		X	
Serum procalcitonin	X		X	
Interleukin 6	X		X	
Serum amyloid A	X		X	
Efficacy evaluation indicators				
Clinical symptom assessment		X-------------------------------------------X		
Clinical symptom improvement rate on day 4		X		
Improvement rate of single symptoms			X	X
CASA-Q	X		X	X
Improved pneumonia Imaging Absorption Evaluation scale	X		X	
CURB-65 score	X		X	
Dosage and course of antibiotics		X	X	X
Changes in inflammatory indicators	X		X	
TCM Syndrome Points		X------------------------------------------X		
Improvement rate of TCM evidence of efficacy		X	X	X
The amount of emergency drug used		X-----------------------------------------X		
Safety evaluation				
Basic vital signs	X	X	X	
Routine blood test	X		X	
Liver and kidney function tests	X		X	
Routine urine test	X		X	
Urine pregnancy test	If necessary			
ECGs	X		X	
Adverse event assessments		X------------------------------------------X		
Other related work				
Subject screen	X			
Random assignment	X			
Drug distribute	X			
Collect blood and sputum samples	X		X	

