This study has several limitations. Firstly, the inherent subjectivity of TCM syndrome assessments may introduce bias. Although all investigators received standardized training and utilized unified evaluation criteria, variations in inter-rater reliability could persist across multiple centers during clinical judgment of symptom patterns. Second, despite rigorous matching of the placebo and YMJD granules in appearance, odor, and taste, potential unblinding might occur if participants perceive differential gastrointestinal effects or treatment onset times. We will statistically evaluate blinding success through end-of-trial participant/investigator questionnaires and sensitivity analyses.

To our knowledge, this is the first large-sample, randomized, double-blinded, placebo-controlled trial to investigate the efficacy and safety of YMJD granules among patients with CAP. We anticipate the results to provide insight into the science of Chinese patent medicine for CAP. Understanding how YMJD can improve early clinical symptom, identify advantageous patients and key stages for treatment, which may inform novel therapeutic approaches in the treatment of patients with CAP.

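### The stated aim of explaining early symptom improvement cannot be met: every post-baseline marker and sample is taken on day 7, after the day-4 outcome

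*Protocol article*

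**What the plan says.** The Discussion paragraph of the abstract states the mechanistic aim: "It aims to elucidate the mechanisms of early symptoms improvement". The closing paragraph of the Discussion (section 3) returns to it: "Understanding how YMJD can improve early clinical symptom".

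The article fixes what early means. In the abstract, "The primary outcome is the clinical symptom improvement rate on day 4". Section 2.5.1.1 defines it as an early clinical response, assessed "within 96 h following the initial dose of study medication", and the Discussion again calls the day-4 assessment the early response.

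Section 2.6 names the means of studying mechanism: "All of biological samples will be used for muti-omics analysis to explore the biological mechanisms of YMJD". On timing, the same section says: "Blood samples (standard EDTA blood collection) will be collected on day 1 and day 7". It gives no days for sputum, but the Table 4 row "Collect blood and sputum samples" is marked at day 1 and day 7 only. For C-reactive protein, procalcitonin, interleukin 6 and serum amyloid A, section 2.5.2.7 says: "Evaluate the improvement of systemic infection indicators in two groups of patients on day 1 and day 7 of enrollment". Table 4 agrees.

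**The concern.** To show that a biological change lies on the path from treatment to an outcome, the change has to be measured after treatment starts and no later than the outcome. Here the only post-baseline biological measurement comes after the outcome. A between-arm difference on day 7 then has at least three possible sources: a process that produced the day-4 response, a consequence of having recovered by day 4, or an effect of the remaining days of treatment. The data cannot tell these apart, and no later analysis can supply the missing measurement.

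At stake is what the trial may conclude about mechanism. A reader of the abstract will expect the omics and marker results to account for the day-4 effect. If day-7 findings are reported under that aim, consequences of recovery could be presented as the way YMJD works.

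**Working it through.** The plan gives no figure on this point. The check is one of timing, setting the sampling days against the outcome day.

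**Inputs**
- Outcome: day 4, within 96 h of the first dose (abstract; section 2.5.1.1).
- Blood: days 1 and 7 (section 2.6; Table 4).
- Sputum: days 1 and 7 (Table 4).
- Four inflammatory markers: days 1 and 7 (section 2.5.2.7; Table 4).
- Visit windows: day 4 ± 1 and day 7 ± 1, stated in section 2.7 for safety assessments. Applying them to the day-4 outcome visit and to the day-7 samples is an assumption.

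**Step 1: nominal gap.** Second sample minus outcome = 7 − 4 = 3 days.

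**Step 2: gap with windows.** The day-4 visit falls on days 3 to 5 and the day-7 sample on days 6 to 8.
- Smallest gap: 6 − 5 = 1 day.
- Largest gap: 8 − 3 = 5 days.

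The order never reverses, and the two never coincide.

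**Step 3: gap against the 96 h limit.** Count day 1 as 0 h.
- Day 7 is (7 − 1) × 24 = 144 h, which is 144 − 96 = 48 h after the limit.
- Day 6, the earliest day under the assumed window, is (6 − 1) × 24 = 120 h, which is 120 − 96 = 24 h after it.

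**Step 4: what is measured after baseline and by day 4.** Table 4 and sections 2.5.2.8 and 2.7 place symptom grades, TCM scores, vital signs, antibiotic and emergency drug use, concomitant medication and adverse events there. These are clinical or treatment records. The number of inflammatory markers or biological samples in that interval is 0.

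**Step 5: what the two sampling days can support.**

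| Question | Supported by day-1 and day-7 samples? |
|---|---|
| Do day-1 markers predict the day-4 response or modify the treatment effect on it? | Yes, as exploratory work |
| Does marker change from day 1 to day 7 differ between arms? | Yes, as a comparison of randomized groups |
| Which biological change produced the day-4 response? | No; nothing is measured in the interval |
| Do day-7 markers relate to day-14 outcomes? | Descriptively only |

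On the last row, day-14 cure (section 2.5.2.1) is resolution of the same four symptoms that are graded on day 4. A patient who improved by day 4 would plausibly have both better day-7 markers and better day-14 status. Earlier recovery confounds the association even though the marker precedes the outcome.

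**The case against.** The strongest reply is that the article plans no analysis linking day-7 markers to the day-4 response. Section 2.5.2.7 evaluates marker improvement in the two groups. Section 2.10.3 models change from baseline by arm, with baseline and stratification factors as covariates. Section 2.6 speaks of the mechanisms of YMJD without tying them to day 4, and the Discussion promises only a before-and-after look at the lung microbiome. The main stated aims are efficacy and safety. Mechanism is not a listed outcome, does not drive the sample size, and any omics plan would normally sit in a fuller document.

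All of that stands, and it limits the point. A reader might infer that the trial intends a mediation analysis in the wrong time order; the article does not say so. A reader might also want a percentage for the share of the treatment effect that a day-7 marker would falsely explain. Such a figure would model an unplanned analysis and rest on marker differences between responders and non-responders that the article does not give, so none is offered. Nor is it right that the samples say nothing about early response, since day-1 values can be studied as predictors or modifiers.

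The reply does not remove the mismatch between the aim and the schedule. Both are stated explicitly in the article, and a fuller analysis plan could not create a measurement that is not taken.

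**Conclusion.** The concern holds as a limit on what the trial can conclude about mechanism. The article aims to explain early improvement, defines early as day 4, and schedules no marker or biological sample between baseline and that day. Day-7 differences between arms can describe what has changed biologically by the end of the 7-day course. They cannot establish how the day-4 response arose.

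The size is best given as timing: no sample in the relevant interval, and a second sample 3 days after the outcome. The range of 1 to 5 days depends on the assumed windows; the nominal schedule does not. The consequence is confined to an exploratory aim and does not touch the primary efficacy analysis. This is a minor, nearly free correction.

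**What to change.** Make three changes of wording, and carry them into any analysis plan and the results report.

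1. In the abstract's Discussion, section 2.6 and the closing paragraph of the Discussion, restate the exploratory aim as between-arm biological change from day 1 to day 7, the end of treatment.
2. State that day-7 markers and omics results will not be interpreted as mediators or mechanisms of the day-4 response.
3. If day-7 markers are related to day-14 outcomes, label the association as descriptive and say that earlier recovery confounds it.

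The cost is a less ambitious mechanistic claim. No new samples, visits or patients are needed. Keeping the early-mechanism claim would instead require a biological measurement at or before day 4. That is an extra procedure, and patients enrolled before such a change would still lack it (enrolment began in January 2023), so it is not proposed here.

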**Ethics and dissemination:**

This study design was approved by the Ethics Committee of Guangdong Provincial Hospital of Chinese Medicine (Reference Number: BF2022-306-01).

**Clinical trial registration:**

https://www.chictr.org.cn/showproj.html?proj=189230, Identifier ChiCTR2300072343.

## Introduction

1

Community-acquired pneumonia (CAP) is one of the primary causes of hospitalization and death from infectious diseases worldwide (1), characterized by lung infiltrates on imaging accompanied by clinical manifestations including fever, dyspnea, and productive cough (2). In China, CAP demonstrates an incidence of 7.13 per 1,000 person-years (3), with median hospitalization costs reaching $556.50 for low-risk cases (4), collectively imposing a substantial health and economic burden. The core principle of CAP treatment is anti-infection, respiratory fluoroquinolones or *β*-lactam/macrolide combination therapy are recommended as first-line regimens (5). However, antibiotic overuse raises concerns about complications, including clostridium difficile-associated diarrhea, gastrointestinal disturbances, and hepatorenal toxicity (6–8), where prolonged regimens escalate adverse event risks. Emerging evidence suggests that *β*-lactam/macrolide combinations have limited efficacy against atypical pathogens in outpatient settings (9, 10), highlighting the need for precision in early therapeutic interventions. Therefore, how to alleviate clinical symptoms and reduce antibiotic use in the early stages of CAP has become the key problem in treatment.

Although Traditional Chinese Medicine (TCM) does not utilize the specific disease name CAP, it categorizes this condition based on its clinical manifestations within the scope of the “cough disease.” According to the Guidelines for Traditional Chinese Medicine Diagnosis and Treatment of Community Acquired Pneumonia (2018 Revision) (11), the pathogenesis of CAP is primarily attributed to two key aspects: (1) exogenous pathogen invasion compromising the lung’s defensive system, or (2) vital qi deficiency impairing resistance against pathogenic factors. The core therapeutic principle focuses on eliminating pathogens and reinforcing vital qi. Emerging evidence supports TCM as a promising adjunct therapy for CAP. Its treatment mechanism include microbial invasion (bacterial, viral, etc.), excessive inflammatory response mediated and oxidative tissue damage (12, 13). The YMJD formula, developed based on the TCM concept of “lung-gut axis coordination,” demonstrates multi-targeted therapeutic effects against these pathological processes. Previous randomized controlled trials (RCTs) demonstrate YMJD’s ability to improve acute bronchitis through inhibitition of inflammatory factors including IL-1β and TNF-*α*, along with improvements in bowel movements and pulmonary function (14, 15). Evidence from experiments has also shown that the components of YMJD granules can reduce the levels of the infiltration of white blood cells, lymphocyte, mononuclear cells and neutrophils, with the inhibition of granulation tissue proliferation in mice (16–18), especially for *Staphylococcus aureus* (19), one of the main pathogen in CAP. Hence, the YMJD granule could potentially serve as a traditional Chinese medicine formula for treating CAP.

Currently, there is a lack of large-scale randomized controlled trials evaluating YMJD granules for CAP under evidence-based principles, particularly regarding early symptom improvement. To address this gap, we will conduct a prospective, multicenter, randomized controlled trial to assess the clinical benefits of combining YMJD granules with standard antibiotics within the critical first 72 h after symptom onset. This study aims to determine the efficacy and safety of YMJD granules in CAP patients while providing high-quality evidence for integrating TCM into CAP treatment strategies.

## Methods

2

### Study design

2.1

This is a randomized, double-blind, placebo-controlled, multicenter study involving 11 hospitals in China. The study flow is designed strictly according to the Consolidated Standards of Reporting Trials (CONSORT) and Standard Protocol Items: Recommendations for Interventional Trials (SPIRIT). It aims to evaluate the safety and efficacy of YMJD granules combined with antibacterial drugs for CAP. Patients and the public were not involved in the design, conduct, reporting, or dissemination plans of our research. The overall flow diagram of the research procedure is shown in Figure 1.

**Figure 1 fig1:**
[figure not shown]
The flow diagram of the trial.

### Study population

2.2

#### Participant recruitment

2.2.1

A total of 226 patients with CAP who meet the eligibility criteria, will be recruited from 11 centers participating in this study. These include one main center, the Guangdong Provincial Hospital of Chinese Medicine, and 10 cooperating centers: Guangdong Second Traditional Chinese Medicine Hospital; The First Affiliated Hospital in Guangzhou University of Chinese Medicine; The Second Affiliated Hospital of Tianjin University of Traditional Chinese Medicine; Shenzhen Traditional Chinese Medicine Hospital; Foshan Traditional Chinese Medicine Hospital; The First Affiliated Hospital of Henan University of Chinese Medicine; The Affiliated Hospital of Jiangxi University of Traditional Chinese Medicine; Guangzhou Panyu District Traditional Chinese Medicine Hospital; Guangdong Qifu Hospital and Huizhou Third People’s Hospital. At each center, a trained study coordinator will identify potentially eligible patients and work with the attending physician to determine their suitability for the trial. Once the patient is confirmed to meet the inclusion and exclusion criteria, they will be enrolled in the trial. Enrolled began in January 2023 and will conclude by December 2027.

#### Inclusion criteria

2.2.2

Each patient had to satisfy the following inclusion criteria before entry into the study:Patients are between 18 and 80 years of age.Meeting the diagnostic criteria for CAP in the “Guideline of Diagnosis and Treatment for Community-Acquired Pneumonia among Adults in China (released in 2016) (20)”.Meeting the “Guidelines for Traditional Chinese Medicine Diagnosis and Treatment of Community Acquired Pneumonia (2018 Revision) (11) for the “*syndrome of wind-heat invading lung*” or “*syndrome of phlegm-heat obstructing lung*” in Chinese medicine (21).The clinical symptoms should manifest as at least 2 of the following 4 main symptoms: cough, expectoration, dyspnea (shortness of breath), and pleurisy chest pain.Patients with CURB-65 score 0–2 (22).Before recruitment, clear notification and signing of informed consent are required.

#### Exclusion criteria

2.2.3

Severe CAP patients.Interstitial pneumonia, viral pneumonia, and hospital-acquired pneumonia (including ventilator-associated pneumonia).Patients with serious complications such as lung abscess, atelectasis and empyema.Patients complicated with other serious respiratory diseases, such as chronic obstructive pulmonary disease, bronchiectasis, and active tuberculosis.Patients combined with severe brain, heart, liver, renal, and blood system diseases, as well as mental illness.Use of Chinese herbal medicine or Chinese patent medicine that have effects of clearing heat and reducing phlegm and relieving cough or had the antibacterial effect clearly defined by modern pharmacology within 48 h prior to enrollment.Liver function (ALT, AST) or kidney function (serum creatinine) exceeds 2 times the upper limit of normal value.One of the following three conditions (23): ① fullness or hidden pain in the stomach and epigastrium, the stomach likes to press and warm, loose stools, weakness, pale tongue with teeth marks on the sides; ② fullness in the stomach and epigastrium, aggravated by cold, noisy acid reflux, dry mouth and bitterness, cold limbs, and loose stools; ③ recurrent loose stools or diarrhea, which may occur or aggravate at the slightest carelessness in diet, pale tongue.Patients with diseases that severely affect the immune system such as malignancy, organ or bone marrow transplantation, HIV infection, or patients taking immunosuppressive drugs or systemic glucocorticoids within the last 3 months.Patients with dysphagia or a history of gastrointestinal disorders that interfere with the absorption of the test drug (including but not limited to chronic diarrhea, reflux esophagitis, ulcerative colitis, intestinal tuberculosis, gastrinoma, short bowel syndrome, post major gastrectomy, etc.).Combined with diabetes and unstable glycemic control before this episode, glycated hemoglobin control target >7%.Previous history of drug addiction or drug abuse.Pregnancy, planned pregnancy or lactation women.Previous history of severe allergic reactions or known history of hypersensitivity to YMJD granules or placebo ingredients.Patients who have participated or are participating in other clinical trials within the last 3 months.Patients who, in the opinion of the investigator, are poorly adherent and have difficulty completing or complying with the requirements of this trial.

